## Analysis of Outcome Measures

As described above, primary and secondary outcomes which are continuous variables will be analysed using linear regression models in an ITT analysis as the primary statistical analysis.

The primary analysis will test for:

- A difference in the change (from baseline to follow up) in % SFA intake between each intervention group compared to control;

- A difference in the change (from baseline to follow up) in % SFA intake between the two active intervention arms.

Using the appropriate interaction terms in the above mentioned models, we will perform subgroup analyses of the primary and secondary outcomes by sociodemographic characteristics (SES), as a previous study has shown that lower SES households purchase a higher proportion of energy from less healthy foods with smaller but important differences in the SFA content from purchased foods which may lead to differential effectiveness^21^. While the study is not powered to look for such effects here, this information will inform planning of subsequent research.

Acceptability of the intervention by the participants will be collected by questionnaire and will be summarised by presenting the frequencies of each response in bar charts.

# DATA MANAGEMENT

## Access to Data

Direct access will be granted to authorised representatives from the Sponsor and host institution for monitoring and/or audit of the study to ensure compliance with regulations.

## Data Recording and Record Keeping

We have discussed the data management and quality assurance of this study with a Senior Trials Manager from the UKCRC registered Primary Care Clinical Trials Unit (CTU). We agreed that they will provide general advice and support to ensure we follow CTU best practice but this study will not formally be adopted in the CTU portfolio. A study specific Data Management Plan (DMP) will be developed for the trial outlining in detail the procedures that will be put in place to ensure that high quality data are produced for statistical analysis.

A secure online database (password protected and kept on secure servers) will incorporate an electronic Case Report Form (CRF) onto which the central research team will enter data. If a paper CRF is needed, the original CRFs will be kept and returned by the central research team to the University of Oxford research base on a lockable briefcase and a copy will be held at the research site. All CRFs (electronic or paper) will be date stamped upon receipt. The central research team will store all paper CRFs and other study data documents, including consent forms, securely at the Primary Care department in a locked cabinet, in a locked room within a restricted access building with keypad access control system. A full pre-entry review and electronic data validation for all data entered into the clinical database will be provided by study specific programmed checks. Data from the dietary questionnaires will be collected and stored independently from the study team by the Cancer Research Unit servers (Nuffield Department of Population Health, University of Oxford) in anonymised form (using a unique study ID for each participant), and will be transferred to the study team only after full consent has been obtained using an encrypted and secure system. If a participant declines consent or is found to be ineligible, their questionnaire data will be deleted by those holding it independently.

On completion of the trial and data cleaning, the study documentation will be transferred to a secure, GCP compliant archiving facility, where they will be held for 5 years. Prior to database lock, a dataset review will be undertaken by the Chief Investigator and the trial statistician.

## Study Management

The Chief Investigator will be responsible for project coordination, and will be the lead trial manager and data analyst. She will be supported by [name] and [name] who will provide expertise in development of complex behavioural interventions in primary care and trial design. A Senior Trial Manager from the UKCRC registered PC-CTU will provide further advice and support to the Chief Investigator throughout the study in relation to trial management and will oversee the operational aspects of the trial. A trial statistician will review and approve the statistical analysis plan and will provide support for the statistical analysis.

# QUALITY ASSURANCE PROCEDURES

## Quality Control and Quality Assurance Procedures

Regular monitoring will be performed. Data will be evaluated for compliance with the protocol and accuracy in relation to source documents where possible. Following the standard procedures specified in the protocol and working instructions, the study members in charge of this will verify that the clinical trial is conducted and data are generated, documented and reported in compliance with the protocol, GCP and the applicable regulatory requirements.

The Trial Management Group (TMG) will be comprised by the Chief Investigator together with the PC-CTU Senior Trial Manager, the senior co-investigators ([name] and [name]), two PPI members, and one independent statistician ([name]). The TMG will be responsible for the monitoring of all aspects of the trial’s conduct and progress and will ensure that the protocol is adhered to and that appropriate action is taken to safeguard participants and the quality of the trial itself. The TMG will meet regularly throughout the course of the trial.

## Risk Assessment

The TMG will conduct a risk assessment and develop a trial specific monitoring plan before the first participant is recruited. The risk assessment will identify any trial specific risks (to both the participants’ safety and well-being and the integrity of the trial data).

Based on the outcome of this assessment, a trial specific monitoring plan will be developed to detail strategies to be employed to minimise the trial specific risks identified.

## Trial Steering Committee / Data Monitoring Committee

Due to the low risk nature of the PC-SHOP trial and that it is an open label trial, the Trial Management Group will act as the Trial Steering and Data Monitoring Committee to provide oversight of all matters relating to participant safety and data quality.

# ETHICAL AND REGULATORY CONSIDERATIONS

## Declaration of Helsinki

The Chief Investigator will ensure that this study is conducted in accordance with the principles of the Declaration of Helsinki 2013.

## Guidelines for Good Clinical Practice

The Chief Investigator will ensure that this study is conducted in accordance with relevant regulations and with Good Clinical Practice.

## Approvals

The protocol, informed consent form, participant information sheet and any other relevant intervention materials will be submitted to an appropriate Research Ethics Committee (REC), and host institution(s) for written approval.

The Chief Investigator will submit and, where necessary, obtain approval from the above parties for all substantial amendments to the original approved documents.

## Reporting

The CI shall submit once a year throughout the study, or on request, an Annual Progress report to the REC Committee, host organisation and Sponsor. In addition, an end-of-study notification and final report will be submitted to the same parties.

## Participant Confidentiality

Data will be kept in accordance with the Data Protection Act (DPA) 2018. We have discussed the data management and quality assurance of this study with a Senior Trials Manager from the UKCRC registered Primary Care Clinical Trials Unit (CTU). We agreed that they will provide general advice and support to ensure we follow CTU best practice but this feasibility study will not be formally adopted in the CTU portfolio. Participant identifiable information will be available to the person conducting follow ups as it is important that these data are known to them. Otherwise, confidentiality will be maintained and no-one outside the study team will have access to either the CRFs or the database.

Participants will only be identified on study documents by use of a unique study ID which cannot be used to identify individual participants. The central research team will store all CRFs and other study data documents, including the consent form, securely prior to data entry in a locked cabinet, in a locked room within a restricted access building with keypad access control system. CRFs and all other documents holding participant identifiable information will be anonymised as soon as possible with the process of management being outlined in detail within the ethics application and in the Data Management Plan.

Participant identifiable data will be required for the duration of the trial due to the intervention and trial procedures. Contact information will be destroyed at the end of the study. Participants will be identified in study documentation only by a unique identifier.

The database without contact details will be anonymised and a secure compact disc containing the link between identification number and participant identifiable information will be stored in a secure archiving facility.

The central research team will need to share the participant's name and clubcard number with the commercial partner (Tesco) so that the central research team can access the participant’s shopping data, which is needed to deliver the intervention. No other information will be shared with Tesco.

The trial management team will monitor confidentiality and consent will be sought from participants for the PC-SHOP research team to have direct access to participant medical records.

The study coordination centre will obtain approval from the Health Research Authority (HRA).

## Expenses and Benefits

As a result of participation in the PC-SHOP trial participants, will be asked to attend 2 or 3 study visits at their local GP practice. In order to minimise the burden on participants of claiming travel expenses (providing receipts, recording mileage, completing forms) the central research team will offer each participant a £10 gift card at the 3-month study visit.

For the qualitative sub-study, a £20 gift card will be provided by post after the interview has been completed.

# FINANCE AND INSURANCE

## Funding

This study will be funded by the National Institute for Health Research (NIHR) Collaboration for Leadership in Applied Health Research and Care Oxford at Oxford Health NHS Foundation Trust. The research funding will be administered by the administrative and finance teams within the Nuffield Department of Primary Care Health Sciences.

## Insurance

The University of Oxford will act as Sponsor for the PC-SHOP trial.

The University has a specialist insurance policy in place which would operate in the event of any participant suffering harm as a result of their involvement in the research (Newline Underwriting Management Ltd, at Lloyd’s of London).

# PUBLICATION POLICY

The investigators within the central research team will be involved in reviewing drafts of the manuscripts, abstracts, press releases and any other publications arising from the study. The main paper reporting the primary outcome will also include data on the secondary outcomes. Other qualitative outcomes, including acceptability of the intervention, may be reported in additional papers.

The trial results will be published and all who meet the criteria for authorship will be listed as authors. Authorship will be determined in accordance with the ICMJE guidelines and other contributors will be acknowledged.

We will submit the paper to NIHR for approval before submission.

# APPENDIX A: STUDY FLOW CHART

[figure not shown]

# APPENDIX B: SCHEDULE OF STUDY PROCEDURES

|  | **Baseline**  **visit 1** | **Baseline**  **visit 2** | **Month 3**  **visit** |
| --- | --- | --- | --- |
| **Length of visit** | 60 min | 15 min | 45 min |
| **Who conducts** | Central research team | Health  professional | Central research team |
| **Procedures** |  |  |  |
| Informed consent | √ |  |  |
| Eligibility assessment | √ |  |  |
| Randomisation | √ |  |  |
| Demographics/shopping behaviours | √ |  | √ |
| Medical history | √ |  | √ |
| Weight and height | √ |  | √ |
| Blood pressure | √ |  | √ |
| Blood sample | √ |  | √ |
| Medication review | √ |  | √ |
| 24h dietary recall | √ |  | √ |
| Tesco’s club card number | √ |  | √ |
| Questionnaires about the intervention | √ |  | √ |
| Intervention delivery |  | √ |  |

#

# APPENDIX C: QUALITATIVE SUB-STUDY TOPIC GUIDE

INTRODUCTION

“Hello, this is <<Researcher Name>> calling from the PC-SHOP study. Am I speaking with <<Participant Name>>?

You recently participated in our study and kindly agreed to tell us your experiences of trying to reduce the amount of saturated fat you were eating.

As a quick reminder, the study involved advice from the nurse at your GP surgery and some suggestions for healthier swaps based on the types of food you usually purchase. Does that sound familiar?

Some people have found having the British Heart Foundation leaflet and their shopping report in front of them helpful to jog your memory. If you have yours on hand, that would be great. But not a worry if not.

I’m going to ask roughly 10 questions about your experience of the study. These questions will help us cover everything and make sure that we do not overrun. This call should not last any longer than 30 minutes.

If you are agreeable, I will also record this call to allow us to analyse what you said in detail. Is it OK if I press record now?

NB: IF YES, RESEARCHER SHOULD PRESS RECORD HERE

NB: IF NO, RESEARCHER SHOULD THANK PARICIPANT AND END THE INTERVIEW NOW WITH AN EXPLANATION FOR THE REASONS WHY.

Please do give me your honest reflections about your experience, warts and all. We will not tell your GP what you say and we really want to hear about your experience to help us improve the support we give to people in the future.

Do you have any questions?

How about I start by asking what prompted you to join the study?”

_________________________________________________________________________

QUESTIONS

| Intervention Components | Questions & Probes | Targeted Determinant | Intervention Function |
| --- | --- | --- | --- |
|  | What’s your understanding about the effects fat can have on your health?  Probes:  How do you think the fat in your food might affect your health?  How do you think about the cholesterol in your blood and its effects on your body? | Knowledge  Health Values | Education |
| BRIEF ADVICE SESSION DELIVERED BY A PRACTICE NURSE | | | |
| Discussion of CVD risk and motivational advice | What did you think about the advice you received from the nurse?  Probes:  What do you remember the nurse discussing about your recent blood results?  Did you feel there were important issues that weren’t discussed in this session? Give examples. | Knowledge  Health Values | Education  Persuasion |
|  | Did you try to make any changes to your diet after speaking with the nurse?  Probes:  In what ways did you think differently about your food when you went shopping?  How encouraged were you to start changing your diet?  If you didn’t change anything, what do you think is the reason for that? | Health Values | Education  Persuasion |
| BHF Leaflet | What did you think about the British Heart Foundation leaflet?  Probes:  How did it help your understanding about fat in your diet?  How motivated were you to act differently e.g. begin reading food labels, buying different foods? | Knowledge  Skills  Self-efficacy | Education  Persuasion  Training |
|  | Is there any other support your nurse or GP could provide, which you feel would help you to improve your diet?  Probes:  Did you get advice from anyone or anywhere else? If yes, how helpful was that advice? | - | - |
| PERSONALISED FEEDBACK ON FOOD SHOPPING | | | |
| Summary of % SFA in previous food purchases and top 3 foods contributing to SFA | What did you think about the shopping reports?  Probes:  How did you feel about us looking at your food shopping?  Did you find the feedback helpful? | Knowledge  Health Values  Behavioural regulation | Education  Persuasion |
| Suggested swaps | And what did you think about the healthier swaps suggested?  Probes:  Did you try the swaps?  Have you stuck to the swaps?  In what ways did you make any other swaps not suggested in the report?  Were the swaps reasonable in price, taste, appearance or brand prevent or encourage you to change your shopping? | Self-efficacy & behavioural regulation | Education  Training  Enablement |
| CONTEXUAL FACTORS & SUSTAINABILITY | | | |
|  | Was there anything else that influenced your food shopping?  Probes:  What other information would you like to have at hand in order to help you improve your food choices?  Do you feel anyone else in your household affected your shopping choices?  Is anyone else in your household using the swaps suggestions? | - | Contextual Factors and Sustainability |
| FUTURE INTERVENTIONS | | | |
|  | Imagine we ran this study again. How would you feel about health advice coming from someone else other than your GP, for example a supermarket pharmacist? | - | Who and where behaviour is influenced |
|  | Lastly, are there any final thoughts or experiences about the study that you would like to share?  Probe  Are there any bits that you felt worked or really didn’t work?  Do you have any other suggestions on how we could improve this study? | - | - |

“Well that’s the end of this call.

The intention was to discuss your experiences of the PC-SHOP study. To summarise, we spoke about your understanding of saturated fat and its effect on your health, your thoughts on the advice and feedback you received, and some recommendations for future research.

You will shortly receive a £20 store card in the mail, as well as copy of the researcher-initialed consent form.

If you have any questions about this research, please do not hesitate to contact a member of the research team.

Thank you very much for your time. I’ve really enjoyed hearing about your experiences and I hope you’ve enjoyed sharing them with me today. Thank you very much for taking part in this study. Goodbye”.

___________________________________________________________________________

END

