## Qualitative sub-study

This qualitative study aims to conduct a qualitative process evaluation to examine the perceived value of the behavioural change techniques used in the intervention and the perceived impact on food purchasing behaviours through semi-structured, one-to-one, telephone interviews with approximately 28 participants in intervention 2 group.

This qualitative study will play a valuable role as part of the process evaluation of the trial and will help in the interpretation of the findings of the trial. If the trial outcome is promising it may point to areas that could be enhanced ahead of any future definitive trial to test the effectiveness of the intervention to reduce LDL cholesterol.

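### In the interview topic guide the leaflet probe assumes that the leaflet helped, its row has no counter-probe, and one swaps probe assumes that extra swaps were made; neutral wording would cost nothing

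*Protocol*

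**What the plan says.** Section 8.12 of the Protocol (Qualitative sub-study) plans telephone interviews with approximately 28 participants from Intervention 2. One aim is to "examine the perceived value of the behavioural change techniques used in the intervention". The section adds that, if the trial is promising, the interviews may show what to strengthen before a definitive trial.

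The topic guide in Appendix C gives lead questions, each usually followed by probes. The wording at issue is:

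- **Leaflet.** The lead is "What did you think about the British Heart Foundation leaflet". The two probes are "How did it help your understanding about fat in your diet" and "How motivated were you to act differently e.g. begin reading food labels, buying different foods".
- **Swaps.** After an open lead and two probes on whether the swaps were tried and kept, the guide asks "In what ways did you make any other swaps not suggested in the report".
- **Change after the nurse session.** The lead is "Did you try to make any changes to your diet after speaking with the nurse". The probes include "In what ways did you think differently about your food when you went shopping" and "How encouraged were you to start changing your diet", followed by one asking those who changed nothing for the reason.

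**The concern.** A probe that asks how something helped, or in what ways something was done, takes it as given that it helped or was done. A participant who got nothing from the leaflet must contradict the question to say so. In a call made by the study's own research team, some may find it easier to name a benefit.

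The components are also probed unevenly. For the shopping report, the guide asks whether the feedback was helpful. For the nurse session, it asks why nothing changed, if nothing did. The leaflet gets neither. If the interviews are used to say which techniques participants valued, part of any difference between components could come from the wording. What is at stake is how the perceived value of the leaflet is described, and what is kept or strengthened for a later trial.

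**Working it through.** The plan states no figure on this point, so the check is a reading and count of the probes in Appendix C.

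**All probes, row by row:** effects of fat 2, nurse advice 2, changes after the nurse session 3, leaflet 2, other support 1, shopping reports 2, swaps 4, contextual factors 3, final thoughts 2. The sum is 2 + 2 + 3 + 2 + 1 + 2 + 4 + 3 + 2 = 21. The question on future interventions has no probe.

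**The three areas at issue:** nurse advice 2 + 3 = 5, leaflet 2, swaps 4, so 5 + 2 + 4 = 11. Each probe was classed as presupposing benefit or change; graded (how much, in a positive frame); or neutral, two-sided or inviting a negative answer.

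| Area | Probes | Presupposing | Graded | Neutral, two-sided or negative |
| --- | --- | --- | --- | --- |
| Nurse advice | 5 | 1 | 1 | 3 |
| Leaflet | 2 | 1 | 1 | 0 |
| Swaps | 4 | 1 | 0 | 3 |
| Total | 11 | 3 | 2 | 6 |

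So 3 of 11 probes in these areas, and 3 of 21 overall, presuppose benefit or change. The leaflet is the only one of the three areas with no probe in the last column.

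**The three presupposing probes are not equally exposed:**

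- *Leaflet.* The lead is neutral, but neither probe offers a way to report no effect. The graded probe can be answered with none at all, but its frame is favourable. This is the clearest case.
- *Swaps.* The preceding probes ask neutrally about the suggested swaps. None asks whether there were any others, so this probe assumes them. The next probe is two-sided about price, taste, appearance and brand, but it does not address the further swaps.
- *Nurse advice.* The lead is a neutral yes/no question and the list ends with a no-change probe. An interviewer could use one probe after a yes and the other after a no. This is a weak case.

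**The case against.** The best reply is that the guide as a whole does not lead. The lead questions in these areas are open or neutral. The introduction asks for candid accounts, good and bad, and says that the GP will not be told. A nurse-session probe asks what important matters were left out. The closing probes ask what did and did not work and how the study could be improved, and these cover every component, the leaflet included. The guide was piloted. Section 5 also provides questionnaires on whether the leaflet and reports were helpful and clear, and measures uptake of swaps from purchases.

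Most of this stands, and it reduces the concern to a modest risk. What it does not supply is a leaflet-specific invitation to report no effect. Purchase data can check swaps, but not a change in understanding, which the leaflet probe addresses. The questionnaires give some cross-check on the leaflet.

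A reader might infer more than the document supports:

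- *That the process evaluation will come out favourable.* Six of the 11 probes in these areas are neutral, two-sided or invite a negative answer, so the text supports a risk only.
- *That both leaflet probes presuppose benefit.* Only one does; the other is graded.
- *That interviewing Intervention 2 alone hides the tilt.* Another arm interviewed with the same wording would carry the same tilt, so it would not expose it.
- *That analysis can do nothing about it.* Interviews are transcribed verbatim, so coders can see which replies follow a leading probe, although they cannot recover the answer to a neutral one.
- *That every interview is affected, or that the participants with least to say get the leading probes.* The Protocol does not say when probes are used or whether all are read out, and the number of interviews may rise or fall with data saturation.

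**Conclusion.** The point holds in a limited form and is minor. One leaflet probe presupposes benefit in a row with no counter-probe, and one swaps probe presupposes further swaps. The nurse-advice probe is a marginal third. Together they are 3 of 21 probes, with 2 more graded in a positive frame. They may encourage favourable answers about those components, chiefly the leaflet.

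The size of any effect on the themes cannot be estimated from the document. It depends on how interviewers use the probes and how readily participants disagree with a question's premise, and neither is stated. The point touches only the qualitative sub-study; the primary and secondary analyses do not use these interviews.

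**What to change.** Before the interviews start, change Appendix C as follows:

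1. Leaflet: *How, if at all, did the leaflet affect your understanding of fat in your diet?*
2. Swaps: *Did you make any swaps not suggested in the report? If so, which?*
3. Optional, nurse advice: *Did you think differently about your food when you went shopping, or not? In what way?*
4. Repeat in the leaflet row the nurse-advice probe that asks for the reason when nothing was changed.

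Participants who did benefit can still say so.

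The cost is two or three reworded probes and one repeated, with no extra interviews or staff. Section 8.12 starts recruitment to the interviews only after main-study follow-up ends, which leaves room to do this first. It also allows minor edits to the guide, but ties them to unexpected themes found during analysis. This change is better made in advance, so that all participants get the same wording.
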